# Using metagenomic analysis to assess the effectiveness of oral health promotion interventions in reducing risk for pneumonia among patients with stroke in acute phase: study protocol for a randomized controlled trial

**DOI:** 10.1186/s13063-020-04528-3

**Published:** 2020-07-10

**Keywords:** Metagenomic, Next-generation sequencing, Pneumonia complicating stroke, Oral health promotion, Randomized controlled trial

## Abstract

**Background:**

The prevalence of pneumonia complicating stroke in acute phase has a poor prognosis and higher risk for death. Oral opportunistic pathogens have been reported to be associated with pneumonia among people with compromised health. Oral health promotion is effective in reducing dental plaque among patients with stroke, which is considered as reservoirs for oral opportunistic pathogens. This study evaluates the effectiveness of oral health promotions in reducing the prevalence of pneumonia via its effects on composition and relative abundance of oral opportunistic pathogens.

**Methods/design:**

This study is a randomized, single-blind, parallel trial of 6 months duration. The study is being conducted at one of the largest medical teaching hospitals in Hefei, China. A total of 166 patients with stroke and free from any post-stroke complication will be recruited. After enrollment, patients will be randomized to one of the following groups: (1) oral hygiene instruction (OHI) or (2) OHI, 6-month use of powered tooth brushing, and 0.2% chlorhexidine gluconate mouth rinse (10 ml twice daily). The primary outcome is the prevalence of pneumonia complicating stroke. Patients will be monitored closely for any occurrence of pneumonia over the entire period of this trial. Oral rinse samples will be collected at baseline and multiple follow-up reviews (3, 5, 7 days, and 1, 3, 6 months after baseline). Next-generation sequencing will be employed to detect composition and relative abundances of the microorganism in the oral rinse samples. Questionnaire interviews and clinical oral examinations will be conducted at baseline and 1, 3, and 6 months after baseline.

**Discussion:**

The findings of this trial will provide evidence whether oral health promotion intervention is effective in reducing the prevalence of pneumonia complicating stroke via its effect on the oral microbiome. The analysis of the outcomes of this trial is empowered by metagenomic analysis at 16S rRNA level, which is more sensitive and comprehensive to help us detect how oral health promotion inventions affect the oral microbiome in terms of its composition, relative abundance, and interactions between species, which all may contribute to the occurrence of pneumonia complicating stroke.

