The following selection criteria are applied: (1) having onset of stroke within 3 days and free of any post-stroke complication; (2) having moderate to severe functional disability—Barthel Index (BI) scores of < 70; (3) being conscious and respiring voluntarily without ventilator; (4) not having any lung disease and lower respiratory infection; (5) not having indwelling naso-gastric feeding tubes; (6) having dysphagia as shown by Gugging Swallowing Screen (GUSS) test; (7) having normal cognitive ability or mild impairment—Mini-Mental State Examination (MMSE) > 18; (7) having the ability to follow instructions (as an assessment of compliance of oral health intervention); (8) not having systemic administration of antibiotics; and (9) not being edentulous. Patients who meet the above selection criteria will be provided with detailed information regarding potential benefits and adverse effects of the interventions, the procedures of this trial, and the anticipated outcomes. They will be asked by a researcher in our team to sign on a written informed consent before enrolling in this study (written informed consent, additional file 3).

According previous studies [12, 13], pneumonia complicating stroke usually occurs within 1 week after stroke. We set the prevalence of pneumonia within 1 week after onset of stroke as the primary outcome of this study since we would like to explore whether oral health promotion interventions could possibly reduce the prevalence of pneumonia after stroke. According to previous epidemiological studies, the prevalence of pneumonia complicating stroke is 20 to 60% [12, 13]. Thus, we hypothesize that in the comparison group, the prevalence of pneumonia complicating stroke within 1 week is 40%, while the prevalence could be decreased to the lower limit of 20% in the interventional group. We set the statistical power at 80% and the statistical significance level at 0.05. Anticipating a 10% dropout rate over the first week of this clinical trial, the initial sample size for each group is proposed as 83 patients per group (166 subjects in total, Gpower 3.0.10 statistical software).

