#### Data management

The principal investigator will oversee the data collection, entry, analyses, and reporting. Two researchers in our team will conduct data proofreading after the completion of data entry. The data will be securely stored in SPSS files in a computer with a password. The statistics software packages SPSS 25 for Windows (SPSS Inc., Chicago, USA) and QIIME 2 will be used to analyze the data. Per-protocol (PP) will be employed for both primary and secondary outcomes in bivariate analyses. Within- and between-group comparisons will be conducted over the clinical trial period. When the outcome variables are continuous and follow a normal distribution, a paired *t* test for related samples will be performed to determine the significant differences over time within a group. The Student *t* test for independent samples will be performed to compare the mean of the outcomes between the groups at baseline and follow-up reviews. When the outcome variables are continuous but do not follow a normal distribution, the Wilcoxon signed-rank test will be performed to determine the significant differences over time within a group. The Mann-Whitney *U* test will be employed to compare the differences in the rank of outcomes between the groups at baseline and follow-up reviews. When the outcome variables are categorical, the McNemar test will be performed to identify the changes in prevalence over time within a group. The chi-square test will be employed to compare the variations in prevalence between the groups at baseline and follow-up reviews. Regression analyses will be employed to address the effect of confounding factors for outcomes. When conducting the regression analysis, the method of Last Observation Carried Forward (LOCF) will be employed to deal with missing outcomes at follow-up reviews. Linear regression will be adopted when the dependent variables are continuous, and the residuals of the regression followed a normal distribution. Negative binomial regression will be adopted when the distribution of the continuous dependent variables is over-dispersed. Logistic regression will be adopted when the dependent variables are binary.

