It has been proved that oral opportunistic pathogens and aspiration pneumonia have a strong association [11], yet the ways to detect oral opportunistic pathogens in the aforementioned studies were limited in conventional culture and PFGE. The traditional culture method uses several selective culture media and is only able to detect those species which can be cultured. Presumptively, the identification of pure isolates of species on the selective culture medium is based on colony morphology and the Gram stain method, which largely depends on personal experience and subjective judgment. PFGE can only target several suspicious species and identify them qualitatively. Unlike those conventional techniques, NGS is able to assess the phylogenic structure, relative abundance, and correlation network of the whole oral microbial community. The high-throughput sequencing of 16S rRNA genes can usually provide taxonomic resolution of the whole microbial community at the genus or even species level. In this trial, we will employ the change of composition, relative abundance, and correlation network from metagenomic analysis as part of the outcome measures. Compared to conventional microbiological techniques, the outcomes from the metagenomic analysis are more comprehensive and sensitive to reflect how the whole oral microbial community is affected by the oral health promotion interventions, and how the change of the whole oral microbial community is associated with the risk for pneumonia complicating stroke. In this trial, the oral rinse samples will be collected at baseline and multiple times within 1 week after enrollment. These consecutive samples in a short time interval will provide a close observation of the dynamic change of oral microbial community, and possibly reflect the exact status of the oral microbial community before the event of pneumonia if any participant develops pneumonia. The findings of this trial will provide much-needed evidence for medical professionals in the field of cardiovascular diseases to advocate or disregard the inclusion of oral health promotion interventions into multidisciplinary stroke treatment.

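### The abstract promises evidence that pneumonia falls via the oral microbiome, but the stated analyses treat pneumonia and the microbiome as separate outcomes and cannot show mediation

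*Protocol article*

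**What the plan says.** The abstract frames the aim as mediation twice. Its Background says the study evaluates whether oral health promotion works by "reducing the prevalence of pneumonia via its effects on composition and relative abundance of oral opportunistic pathogens". Its Discussion says the findings will bear on whether the intervention "is effective in reducing the prevalence of pneumonia complicating stroke via its effect on the oral microbiome".

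The body is framed differently. The objectives at the end of the Background section and the list under Outcomes give pneumonia and the microbiome as separate items. Metagenomic outcome assessment names t tests, ANOVA or LEfSe for relative abundance. Data management says of categorical outcomes: "The chi-square test will be employed to compare the variations in prevalence between the groups at baseline and follow-up reviews". It adds: "Regression analyses will be employed to address the effect of confounding factors for outcomes". No stated model takes the microbiome as a predictor of pneumonia.

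The main Discussion section does announce a link, namely "how the change of the whole oral microbial community is associated with the risk for pneumonia complicating stroke", and notes that serial samples may capture the microbiome before an event. It gives no method for that link and does not mention adjustment for arm.

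**The concern.** Mediation is a statement about a path: arm changes the microbiome, and that change alters the risk of pneumonia. The two arm comparisons estimate the effect of arm on the microbiome and the total effect of arm on pneumonia. Neither depends on whether the microbiome, given arm, predicts pneumonia. An association pooled over arms does not fill the gap, because arm is a common cause of both variables and can link them with no path between them.

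At stake is the mechanistic message in the abstract. The interventional arm adds powered brushing and a rinse together, so pneumonia could fall by another route, for example through less retained food debris. A trial positive on both outcomes could then be reported as having shown a mechanism that its stated analyses never tested. The primary comparison of pneumonia is not affected.

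**Working it through.** **Inputs from the article (Participants).** Control rate: "in the comparison group, the prevalence of pneumonia complicating stroke within 1 week is 40" per cent. Intervention: "the prevalence could be decreased to the lower limit of 20% in the interventional group". Also "We set the statistical power at 80% and the statistical significance level at 0.05", 10% dropout, and 83 per group.

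**The article's own figure.** 83 per group reproduces as a one-sided, continuity-corrected calculation: 74 per arm, and 74/0.9 = 82.2, rounded up to 83. A two-sided uncorrected calculation gives 82, and 82/0.9 = 91.1, rounded up to 92. Sidedness is a separate matter. Here it only means that 74 (after dropout) and 83 (no dropout) are the sizes to use.

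**Step 1: power of the pneumonia comparison.** For a two-sided, uncorrected chi-square test, power = Φ[(δ − 1.96·√(2p̄(1−p̄)/n)) / √((p₁(1−p₁)+p₂(1−p₂))/n)], with δ = 0.20, p̄ = 0.30, 2p̄(1−p̄) = 0.42 and p₁(1−p₁)+p₂(1−p₂) = 0.24+0.16 = 0.40.
- n = 74: (0.200 − 0.1477)/0.0735 = 0.712, so power is 0.762.
- n = 83: (0.200 − 0.1394)/0.0694 = 0.873, so power is 0.809.

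**Step 2: both comparisons significant, with no mediation.** Let pneumonia depend on arm only. Within arm the two outcomes are then independent, so the joint rate is pneumonia power × microbiome power. The article gives no microbiome shift, SD or power, so the shift d (in SD, one continuous score) is an assumption. Microbiome power is about Φ(d√(n/2) − 1.96).
- d = 0.5, n = 74: Φ(3.04 − 1.96) = 0.86, and 0.86 × 0.762 = 0.66.
- d = 0.5, n = 83: Φ(3.22 − 1.96) = 0.90, and 0.90 × 0.809 = 0.73.
- d of 1 or more: microbiome power is essentially 1, so the joint rate is 0.76 (n = 74) or 0.81 (n = 83).

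Simulation agrees to within a point or two:

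| Assumed shift | 74 per arm | 83 per arm |
|---|---|---|
| 0.5-2 SD | 67-76% | 71-81% |
| 0.3 SD | 34% | 39% |
| none | about 4% | about 4% |

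**Step 3: association pooled over arms, still with no mediation.** With equal arms, the intervention share among pneumonia cases is 0.2/0.6 = 0.333, and among non-cases 0.8/1.4 = 0.571. The mean microbiome score therefore differs between cases and non-cases by (0.571 − 0.333)·d = 0.238·d, although the score has no bearing on pneumonia within either arm. In simulation with 75-83 per arm, this pooled association is significant in the expected direction in about 10% of trials (0.5 SD) to 52% (2 SD).

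**Step 4: adding an arm-adjusted coefficient.** If both arm comparisons must be significant and, in addition, the coefficient of the score in a model for pneumonia that includes arm must be significant in the expected direction, false claims fall to about 2%. Counting either direction, the rate is about 2-4% where the microbiome shifts by arm.

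**The case against.** The strongest reply has four parts.

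- *No decision rule is written.* The abstract promises evidence on whether the mechanism operates and does not say that two significant tests establish it. This stands. A reader might infer that the trial will declare mediation whenever both comparisons are significant; the article does not say so.
- *The microbiome and pneumonia are not handled only separately.* The Discussion section announces an association between them. This stands as a limit on the wording, but no method is given. Nothing shows that arms would be pooled, and nothing shows that they would not.
- *A microbiome shift cannot be taken for granted.* The Background calls chlorhexidine's effect on oral opportunistic pathogens in clinical settings unclear. This stands, and it is why the 0.3 SD and no-shift figures belong beside the larger ones.
- *A mediation model may sit in the analysis plan or full protocol, which are not shown.* So its absence alone is no fault. What remains is a mismatch within the article: an abstract framed as mediation, and objectives, outcomes and analyses framed as separate effects.

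Two further limits apply. The title and the numbered objectives make no claim of mediation. Training is also not a clear rival route, since the comparison group too receives instruction in the one-to-one workshop.

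**Conclusion.** The concern holds as a mismatch between the abstract's mediated claim and the analyses the article states. Following those analyses, no result could support the claim.

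The size is conditional. It assumes a true fall from 40% to 20% running wholly by another route, one continuous microbiome score, two-sided tests, and a reading of mediation from the two arm comparisons. Both would then be significant in about 67-81% of trials at an assumed 0.5-2 SD shift, far fewer at 0.3 SD, and about 4% with none. It is tempting to read the upper figures as the trial's false-positive rate. They are not: they are close to the trial's power for pneumonia, given that the effect is real and the microbiome also moves. The change is worth making because the mechanism is the abstract's headline message and the remedy is cheap.

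**What to change.** Take one of two routes.

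1. **Reword.** In the abstract's Background and Discussion, replace the mediated claim with two separate effects of arm, on pneumonia and on the microbiome. This matches the objectives and Outcomes as they stand. It costs only wording and a more modest message.

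2. **Keep mediation as an exploratory aim and analyse it.** Add to Data management a logistic model of pneumonia on arm, one prespecified microbiome score from the last sample before any event, its baseline value, and a few of the recorded confounders. List the bacterial taxa in the score, because the Background names mostly broad groups and includes yeasts, which bacterial 16S sequencing does not target. State which sample event-free patients contribute. Report the indirect effect with a bootstrap 95% interval, and label it as resting on no unmeasured mediator-outcome confounding. State how pneumonia before the day-3 sample is handled, since those patients have no post-treatment score before the event.

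Under either route, adjust for arm any microbiome-pneumonia association announced in the Discussion section.

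Route 2 needs no new samples. Its cost is a wide interval, since 0.6 × 74 = 44.4 and 0.6 × 83 = 49.8 give only about 45-50 expected events, fewer once those before day 3 are set aside. It also rests on a confounding assumption that the data cannot test.

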**Trial registration:**

ClinicalTrials.gov NCT04095780. Registered on 19 September 2019

## Background

Stroke is defined as a “rapidly developing clinical signs of focal (or global) disturbance of cerebral function, with symptoms lasting 24 h or longer, or leading to death, with no apparent cause other than of vascular origin” [1]. A systematic review published in *The Lancet* (2010) reported that no significant change in the incidence and mortality-to-incidence ratios (MIR) of ischemic stroke has occurred during the last two decades [2], while in contrast, a significant increase of hemorrhagic stroke by 22% (95% CI 5 to 30%) and reduction in MIR by 36% (95% CI 16–49%) were observed in low- and middle-income countries [2]. China has the highest incidence rate of hemorrhagic stroke in the world with 159.81 per 100,000 person-years [2]. As a result of the increased incidence and decreased MIR, greater disease burden would be placed on countries with limited financial resources due to a greater number of stroke survivors and disability-adjusted life years (DALYs) [3].

Following stroke, 85% of the patients have limb dysfunction in acute phase, which makes them unable to perform oral self-care [4]. A meta-analysis found that compared to healthy controls, patients with stroke had significantly increased DMFT, plaque index, probing depth, and clinical attachment loss [5]. Another systematic review summarized that following stroke, patients have reduced lip force and tongue pressure against hard palate and uncoordinated masticatory muscle movement, all of which collectively lead to the difficulties of identifying the location of food bolus and propelling it into the esophagus [6]. Food debris is more likely to be accumulated in the oral cavity, giving rise to the growth of opportunistic pathogens (aerobic and facultatively anaerobic Gram-negative bacilli, yeasts, *Staphylococcus aureus*). Among those hospitalized patients with stroke in Hong Kong, aerobic and facultatively anaerobic Gram-negative bacilli (AGNB) was isolated among 72.8% of them [7], and yeast was isolated among 55.4 to 59.3% of them [7, 8]. Among those patients with stroke during the rehabilitation period, the prevalence of AGNB still maintains at the level of 47.9% and yeasts at the level of 50.5% [9]. All the aforementioned reflected a higher prevalence of opportunistic pathogens isolated from patients with stroke than healthy subjects [10]. It has been reported that those opportunistic pathogens are associated with aspiration pneumonia. One study recovered pathogens from the protective bronchoalveolar lavage fluid (PBAL) and compared those pathogens to those isolated from dental plaque by pulsed-field gel electrophoresis (PFGE). A number of *S. aureus* and Gram-negative bacilli isolates in PBAL matched genetically those from the corresponding dental plaque [11]. It is thus posited that the oral cavity can be a reservoir of respiratory pathogens responsible for pneumonia among those people with systemic diseases.

The prevalence of pneumonia complicating stroke in acute phase is ~ 20 to 60% [12, 13]. Although it is not the most frequent medical complications following stroke, it may be the most difficult to manage and has a very poor prognosis, leading to a threefold risk of death [14, 15]. Although it occurs most often within 1 week after the onset of stroke, yet it can still develop in 6 to 30 months after stroke [13]. Prophylactic use of antibiotics to reduce the incidence rate of stroke-associated pneumonia has proved to be of little use in a multi-center randomized controlled trial [16]. Therefore, new preventive approaches for stroke-associated pneumonia aiming at reducing respiratory pathogens in the oral cavity are urgently needed.

Oral health promotion is a range of activities which enable individuals and communities to increase control over the determinants of oral health and thereby improve their oral health. Since dental plaque is associated with many oral diseases, the major composition of oral health promotion interventions aims at removing dental plaque. Dental plaque removal measures include mechanical and chemical measures. Powered tooth brushing has been proved to be more effective than manual tooth brushing in reducing plaque and gingivitis [17]. Chlorhexidine is the gold standard among those chemical plaque control measures, and its antiplaque effectiveness has been well established [18]; however, its effectiveness against oral opportunistic pathogens in the clinical setting is unclear [9].

Moreover, oral health-related quality of life (OHRQoL) reflecting an interaction between oral health conditions and their contextual cultural factors is now recognized as an important parameter in outcome assessment of oral health in epidemiological studies and clinical trials. OHRQoL consists of functional (biting, chewing, swallowing, and speaking) and psychosocial wellbeing (concerns about certain oral conditions and satisfaction with respect to oral care and self-image of appearance) [19]. Therefore, it is also critical to assess the effectiveness of oral health promotion intervention in improving subjective oral health among patients with stroke.

Next-generation sequencing (NGS) technique at the 16S rRNA level will be employed in this proposed trial to assess the change of the composition and relative abundance in the oral microbial community. NGS technique enables us to sequence a great number of genes at one time and profile taxonomic composition at the genus or species level with a deeper coverage of microbial community [20].

We proposed this randomized controlled, parallel, single-blinded, equivalence trial with an allocation ratio of 1:1, which compares the effectiveness of powered tooth brushing with adjunctive use of chlorhexidine mouth rinsing and oral health instruction (OHI) versus OHI in (1) reducing the prevalence of aspiration pneumonia complicating stroke, (2) changing the composition and relative abundance in the oral microbial community, (3) improving oral hygiene status in terms of reducing dental plaque and gingival bleeding, and (4) improving oral health-/generic health-related quality of life.

